### Recruitment {15}

The study will enroll participants from the outpatient routine care facilities in the Capital Region of Denmark and the North Denmark Region (early intervention services (OPUS teams) or Flexible Assertive Community Treatment teams (F-ACT teams)). Patients meeting the listed criteria will be approached about participating in this clinical trial. To avoid unintentional recruitment bias, assessors will regularly attend conferences at the recruitment sites and present the trial as well as invite clinicians to discuss potential referrals.

## Methods: assignment of interventions

### Sequence generation {16a}

Patients providing written informed consent and fulfilling criteria for participation after baseline assessment are allocated to either CBT-VR or CBT. Randomization is performed by a centralized, concealed computer-generated randomization system in REDCap (see Data management section). Block size is created by an independent statistician and will be unknown to the trial assessors and clinicians in the outpatient routine care facilities. The randomized intervention allocation is concealed until the statistical analyses of the resulting data have been completed. Randomization will be stratified by gender, study site, and symptom severity of paranoid ideation (dichotomized as a GPTS Part B score of ≥45 or <45 [3]).

### Concealment mechanism {16b}

Trial assessors write to a specific e-mail when participants have finished baseline assessment and are ready for randomization and treatment allocation. Assessors receive an informatory e-mail, confirming that their e-mail has been received (closed loop communication). One of the therapists has been given the task of performing the allocation sequence and has exclusive access to the randomization program in REDCap (see the “Data management” section), and treatment allocation is thereby concealed for assessors who remain blinded.

### Implementation {16c}

Allocation sequences are generated by the abovementioned therapist with extended access in REDCap at each study site. Enrolment of participants and the intervention assignment will be performed by the therapist who will oversee the given therapeutical course.

## Assignment of interventions: Blinding

### Who will be blinded? {17a}

Independent investigators will conduct the assessments. These trial assessors will be blinded to the treatment allocation of the participants. Due to the nature of the intervention, participants, therapists performing the treatment, and clinicians in charge of TAU will not be blinded to the treatment received. Blinds are maintained by physically separating assessors from therapists performing the treatment. Participants will be instructed not to disclose their allocation prior to assessments continuously through the trial, both orally and in writing. In case an assessor is unblinded, the assessment will be conducted by another blinded trial assessor.

### Procedure for unblinding if needed {17b}

Emergency unblinding of trial assessors is not considered necessary as there is continuous communication between participants, trial therapists, and clinicians in charge of TAU in routine care settings during the trial intervention.

## Methods: Data collection and management

### Plans for assessment and collection of outcomes {18a}

Assessment will be conducted at baseline, treatment end (3 months post baseline), and then 9 months post baseline. To limit the time required to complete the assessments, 5–6 surveys, depending on whether it is baseline or follow-up, will be digitally sent to the participant prior to each assessment with instructions to complete the assessments before the scheduled visit.

The assessors will be psychologists or medical doctors. All assessors will receive adequate training prior to conducting the assessments. The assessors will attend approximately monthly inter-rater reliability training on key measures in the battery and supervised sparring will be performed on weekly basis.

### Plans to promote participant retention and complete follow-up {18b}

Patients participating in the study will be contacted by telephone one week prior to the planned follow-up assessments. Furthermore, clinicians managing the patient’s TAU can help motivate participants to complete follow-up assessments. Assessors are flexible and can rearrange the scheduled time if needed. In case a participant meets discontinuation or exclusion criteria during the study or leaves the intervention program prematurely, clinical and functional assessments will still be performed, if possible.

### Data management {19}

The assessors will enter data from the patient interview directly into the electronic CRF (Case Report Form) using the data entry system REDCap. REDCap is an electronic data capture tool hosted at CIMT in the Capital Region of Denmark [54]. When necessary, the collection will be done in paper and later entered electronically. In REDCap, surveys can be digitally sent to E-boks and the completed form can be returned digitally reducing risk of data loss and leak. E-boks is a public Danish mailing system all inhabitants are in possession of where person sensitive information can be sent safety. REDCap has a complete audit trail on all data transactions, detailed user rights and access control management and thereby complies with Danish legislation (Databeskyttelsesforordningen). Data for each patient is connected to a unique serial number. Only assigned researchers can access REDCap with all the data. Data on paper is stored locally and secured. Research data will be exported from REDCap without personal identifiers. Data will be exported to all well-known software packages: (SPSS, SAS, Stata, R.) and put in logged folders on a network drive under the control of the Capital Region of Denmark, CIMT [54]. A data manager will ensure that all variables are properly defined with variable and value labels. All derived variables will be properly defined, and algorithms will be kept in special files. All data will be examined carefully to identify errors in data entry.

### Confidentiality {27}

Communication between trial researchers and clinicians in charge of TAU in the outpatient routine care settings takes place through a secured e-mail system used elsewhere by clinicians in the Danish Public Healthcare System when communicating person-sensitive information. Collection and maintenance of personal information are described in the abovementioned Data management section.

### Plans for collection, laboratory evaluation, and storage of biological specimens for genetic or molecular analysis in this trial/future use {33}

N/A; no biological specimens were collected as part of this trial.

## Statistical methods

### Analysis of outcomes {20a}

The planned comparisons between the two groups on continuous outcomes will be carried out with a generalized linear model adjusted for stratification variables, potential baseline imbalances, and skewed attrition, with missing data handled by multiple imputations. As an important secondary assessment of this type of outcome, linear mixed model analyses with repeated measurements and an unstructured covariance matrix will assess the interaction term between time and intervention. All analyses will be according to the intention-to-treat principle, analyzing all participants in the groups they were assigned to by randomization; that is all participants irrespective of whether they attended follow-up assessments or not. Primary efficacy analyses will be conducted by a blinded and independent statistician that has no contact with participants in the trial.

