### Outcomes {12}

#### Primary outcome

Level of ideas of social reference is measured with the GPTS ideas of social reference subscale at the cessation of treatment at 3 months. The GPTS is a self-report and has displayed good reliability and validity in patients with psychosis and has also been used in patients at-risk for psychosis showing subthreshold psychotic symptoms (i.e., patients with schizotypal-like symptomatology) [3, 22, 32].

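### The primary model's covariates depend on observed imbalance and attrition, and baseline GPTS-A is not named, so the primary estimate is not fixed in advance and available precision is not guaranteed

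*Protocol article*

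**What the plan says.** The primary outcome is GPTS-A at 3 months. The section on the primary outcome reads: "Level of ideas of social reference is measured with the GPTS ideas of social reference subscale at the cessation of treatment at 3 months".

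Analysis of outcomes {20a} sets the model: "The planned comparisons between the two groups on continuous outcomes will be carried out with a generalized linear model", which is to be "adjusted for stratification variables, potential baseline imbalances, and skewed attrition, with missing data handled by multiple imputations". A mixed model follows, labelled as a secondary assessment: "linear mixed model analyses with repeated measurements and an unstructured covariance matrix will assess the interaction term between time and intervention". The same section adds: "Primary efficacy analyses will be conducted by a blinded and independent statistician that has no contact with participants in the trial".

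The stratification variables are in Sequence generation {16a}: "Randomization will be stratified by gender, study site, and symptom severity of paranoid ideation (dichotomized as a GPTS Part B score of ≥45 or <45". The severity stratum is therefore a dichotomy of Part B, not a measure of Part A.

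Baseline GPTS-A should exist for everyone. A GPTS total score of at least 40 is an entry criterion (Table 1), and Plans for assessment and collection of outcomes {18a} schedules a baseline visit for all: "Assessment will be conducted at baseline, treatment end (3 months post baseline), and then 9 months post baseline". The article does not name it as a covariate.

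**The concern.** The sentence in {20a} does more than leave a covariate list for later. It states a rule, and two of its three parts can be applied only after data are seen: imbalance once baseline is compared by arm, and skewed attrition once follow-up is complete. There is no list of candidate variables, no threshold for imbalance and no definition of how attrition enters. An analysis plan that follows the sentence inherits the open rule; one that fixes the covariates departs from it.

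Two things are at stake. First, the primary estimate, its standard error and its p-value depend on a choice that is still open when the data arrive. Under randomization, a baseline imbalance is chance. What makes a covariate worth including is its relation to the outcome, and that can be judged beforehand. Second, the baseline of the outcome, usually among the best predictors of its follow-up value, enters for certain only through a yes/no split of the other subscale. The sentence covers continuous outcomes generally, so the secondary outcomes are affected in the same way.

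**Working it through.** **1. The plan's own figure.** Inputs from Sample size {14}: difference 5.5, SD 15.5, two-sided alpha 0.05, 128 per arm.

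- SE = SD × sqrt(2/n) = 15.5 × sqrt(2/128) = 15.5 × 0.125 = 1.94.
- Power = Φ(5.5/1.94 − 1.96) = Φ(0.88) = 0.81.

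The stated 81% and 128 per arm are reproduced as an unadjusted comparison with complete data. (5.5/15.5 is 0.355, not the stated 0.33. That is a separate matter; 5.5 and 15.5 are used here.)

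**2. The fair comparator.** The plan already adjusts for the Part B stratum, so the gain from baseline GPTS-A must be counted from there. The residual SD is 15.5 × sqrt(1 − R²). The article gives no correlations, so these are assumed: 0.5 between baseline and 3-month GPTS-A, 0.7 between baseline A and B, 0.4 between baseline B and 3-month A, with the Part B cut near the median. A median split keeps 2/π = 0.64 of the squared correlation.

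- Stratum only: R² = 0.64 × 0.4² ≈ 0.10. Residual SD 15.5 × sqrt(0.90) = 14.70, SE 14.70 × 0.125 = 1.84, power Φ(5.5/1.84 − 1.96) = Φ(1.03) ≈ 0.85.
- Stratum plus continuous baseline GPTS-A: R² ≈ 0.25. Residual SD 15.5 × sqrt(0.75) = 13.42, SE 13.42 × 0.125 = 1.68, power Φ(5.5/1.68 − 1.96) = Φ(1.32) ≈ 0.90 to 0.91.

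**3. Range.** Assumed A–B correlation 0.6 to 0.8, with B related to the outcome only through A:

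| Baseline to 3-month correlation | Power, stratum only | Power, baseline GPTS-A added |
|---|---|---|
| 0.4 | 0.825 to 0.835 | 0.87 |
| 0.5 | 0.832 to 0.850 | 0.91 |
| 0.6 | 0.842 to 0.867 | 0.94 |

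The gain runs from about 4 to about 10 percentage points.

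**4. Type I error.** Two simulations under the null, 256 patients. Simulation A had 10 baseline variables, with coefficients 0.5 for one and 0.15 for nine. Simulation B had 3 or 5 variables, with coefficients 0.5 for one and 0.2 for the others.

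| Rule | A | B (3 / 5 variables) |
|---|---|---|
| Fixed in advance (A: baseline of the outcome; B: all variables) | 4.8% | 5.3% / 5.1% |
| Add only variables imbalanced at p < 0.05 | 4.1% | 3.9% / 4.0% |
| Most favourable of four imbalance cut-offs | 6.0% | not run |
| Most favourable subset of covariates | not run | 10.5% / 14.7% |

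Runs: 4,000 per setting, except 6,000 for the p < 0.05 rule in A. With 4,000 runs the Monte Carlo standard error near 5% is sqrt(0.05 × 0.95/4000) = 0.3 points. The last two rows are what the wording leaves open; the plan describes neither.

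**5. How often the clause would come into play.** The outcome lists name about 20 measures that could be taken at baseline. If all were, and were independent, the chance that at least one differs at p < 0.05 is 1 − 0.95^20 = 64%. Correlation between measures would lower this.

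**The case against.** The strongest reply is that this is one condensed paragraph of an article, and that the full covariate list may sit in an analysis plan that is not shown. For baseline GPTS-A that stands in part. A reader might infer that the plan excludes it, but the text only fails to name it. It could enter through the imbalance clause, the imputation model or the analysis plan, and the secondary mixed model would ordinarily use the baseline measurement. The defensible statement is that its inclusion in the primary model is not guaranteed. The reply does not answer the imbalance and attrition clauses, which are stated rules.

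Second, the primary analysis is assigned to a blinded, independent statistician, and {16a} keeps allocation concealed until the analyses are done. This limits steering towards a preferred arm, so a reader who infers an inflated error rate goes beyond the text: the plain imbalance rule gives about 4%. Blinding does not settle which covariates are used, though, and imbalance can be seen with masked arm codes.

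Third, a reader might take the attrition phrase to mean that a post-randomization variable is put into the outcome model. The more natural reading is adjustment for baseline variables related to differential dropout, which is legitimate if data are missing at random. What stands is that those variables are not identified, and that the planned multiple imputation is a natural place for them.

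Fourth, a reader might quote the gain as 81% to 90%. That ignores the stratum adjustment already planned; about 85% to 90% is the fair comparison.

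**Conclusion.** The concern holds in limited form. The primary model is not fixed in advance, because the text makes adjustment depend on observed imbalance and attrition without a criterion. The precision from baseline GPTS-A is available but not assured.

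The size is moderate. Under the central assumptions, power for 5.5 points at 128 per arm is about 85% as written and about 90% with baseline GPTS-A, and the SE falls from 1.84 to 1.68 points. These figures rest on assumed correlations and complete data. Applied literally at p < 0.05, the imbalance rule is slightly conservative; error above 5% needs favourable picking, which the plan does not describe and the blinded statistician limits.

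The documents do not support reading this as a biased estimate or an invalid sample size. The stated N reproduces without any baseline adjustment, and leaving a prognostic covariate out of a randomized linear comparison costs precision only. It should be fixed as a free improvement; it is not a flaw that invalidates the trial.

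**What to change.** Replace the adjustment phrase in {20a} with a fixed model, along these lines:

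- Primary analysis: linear model for 3-month GPTS-A with treatment arm, continuous baseline GPTS-A, gender, site and the GPTS Part B stratum. No covariate is added or dropped because of observed imbalance.
- Secondary continuous outcomes: the same form, each with its own baseline value where measured.
- Attrition: baseline predictors of dropout enter the already planned multiple imputation as auxiliary variables.
- Any imbalance-adjusted model is reported as a labelled sensitivity analysis.

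The cost is wording in the protocol or analysis plan, settled before unblinding and recorded on the trial registration as the article promises for deviations. No new data and no change to the sample size are needed.

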### Interim analyses {21b}

N/A; no interim analyses are conducted in this trial.

### Methods for additional analyses (e.g., subgroup analyses) {20b}

N/A; no subgroup analyses are conducted in this trial.

### Methods in analysis to handle protocol non-adherence and any statistical methods to handle missing data {20c}

We expect to encounter missing data, and this will be handled with the linear mixed models and multiple imputations as appropriate.

### Plans to give access to the full protocol, participant level-data and statistical code {31c}

No later than 5 years after finishing the last 9 months post baseline interview, we will deliver a completely deidentified data set to an appropriate data archive for sharing purposes.

## Oversight and monitoring

### Composition of the coordinating center and trial steering committee {5d}

The trial will be overseen by a Project Management Group (PMG). The PMG will be comprised of the Primary Investigator (PI) of the study, the daily leader of the trial, the principal therapist of the trial and representatives from each of the sites conducting the study, i.e., the Capital Region of Denmark and the North Denmark Region. The PMG will have a videoconference approximately every month during the recruitment period.

### Composition of the data monitoring committee, its role, and reporting structure {21a}

As the trial has minimal risks, there will be no Data Monitoring Committee (DMC).

### Adverse event reporting and harms {22}

The only known common side-effect of VR is cybersickness, which can be compared to common motion sickness. If encountered, it typically resolves after only a few VR exposures as tolerance occurs. Psychotherapy in VR is generally considered well-tolerated [55]. Hence, we do not expect any serious adverse events to occur. The listed possible serious adverse events are monitored throughout the study: (1) hospital admissions, (2) suicide attempts, 3) any violent incidents necessitating police involvement (whether victim or accused), (4) self-harming behavior, and (5) all deaths.

### Frequency and plans for auditing trial conduct {23}

The PI of this study is a member of the PMG thus making sure information regarding trial conduct is shared across groups. Thus, at least on a monthly basis information regarding the trial is shared.

### Plans for communicating important protocol amendments to relevant parties (e.g., trial participants, ethical committees) {25}

All protocol amendments need to be approved by the Committee on Health Research Ethics of the Capital Region Denmark. Deviations from the published protocol will be documented on the trial registration on ClinicalTrials.gov (NCT04902066).

### Dissemination plans {31a}

Study results will be disseminated to the scientific audience, the public, and trial participants, who through their written consent have expressed a desire to be informed. Discussions regarding the study and its results will be shared in journal publications, conference presentations, and clinical interest groups but also importantly in relevant patient interest groups.

## Discussion

To the best of our knowledge, this will be the largest RCT comparing therapist-guided VR-CBT with standard therapist-guided CBT for paranoid ideations. Initial evidence has revealed VR-CBT to be superior to waitlist control and unguided VR exposure [21, 22]. This trial will further advance knowledge in the field by comparing VR-CBT with the current gold standard of psychotherapeutic treatments for paranoid ideations, which is standard, symptom-specific CBT. While standard, symptom-specific CBT may significantly improve outcomes for paranoid ideations [19], we believe that a more efficient behavioral component, which VR-CBT is believed to generate, is essential in therapy to achieve a greater treatment effect and secondly improve cost-effectiveness. Notably, VR exposure allows for capturing the momentary experiences (thoughts, emotions, and actions) that most closely reflect the real-life situations that trigger paranoid thoughts. This opens for far-reaching possibilities in therapy perhaps not yet fully utilized.

While preliminary evidence exists on the effect of VR-CBT in established psychotic disorders [22], this will be the first RCT to evaluate the effect of VR-CBT for patients with schizotypal disorder displaying less formalized paranoid ideas (e.g., ideas of social reference). Hence, the trial will provide important evidence on the efficacy of VR-CBT for a wider group of patients with psychosis spectrum disorders shedding light on the applicability of therapy to a larger target group.

Additionally, our study clarifies potential mediators and moderators of treatment response that may aid in further identifying the clinical target group for this intervention. The assessment battery in the trial comprises several social cognitive tasks tapping different aspects of social cognition. The trial will therefore add knowledge of the potential cognitive benefits of this treatment [56]. Finally, qualitative analyses are planned which may elucidate possible mechanisms of change along with the efficacy of the specific elements in the VR-CBT protocol (e.g., use of worst-case scenarios, more realistic role-plays, and replaying the same situation but introducing alternative thoughts and behavior)

In sum, our trial will provide highly needed knowledge on the efficacy, cost-effectiveness, and acceptability of VR-CBT for paranoid ideations that may inform clinical practice.

## Trial status

Study protocol, revised version for submission, 25th of July, 2022.

Initial release 9th of April 2021.

Approximately 105-110 participants are included in our study at time of submission. 256 are to be included in total.

Approximate date when recruitment will be completed is the end of September 2023.

## Data Availability

The datasets from the study will be available from the corresponding author on reasonable request.

## Abbreviations

RCT: Randomized clinical trial
VR: Virtual reality
CBT: Cognitive behavioral therapy
VR-CBT: Virtual reality-based cognitive behavioral therapy
TAU: Treatment as usual
GPTS: Green Paranoid Thought Scale
SIAS: Social Interaction Anxiety Scale
PSP: Personal and Social Performance scale
SBQ: Safety Behavior Questionnaire
ERT: Emotion Recognition Task
SAPS: Scale of Assessment of Positive Symptoms
BNSS: Brief Negative Symptom Scale
CDSS: Calgary Depression Symptom Scale
SIDAS: Suicidal Ideation Attribution Scale
COGDIS: Cognitive Disturbance scale
DACOBS: Davos Assessment of Cognitive Biases Scale
GSE: General Self-Efficacy scale
IBT: Intentionality Bias Task
SSPA: Social Skills Performance Assessment
TALE: Trauma And Life Events checklist
R-GPTS: Revised Green Paranoid Thought Scale
CSQ: Client Satisfaction Questionnaire
SD: Standard deviations
PI: Principal Investigator
PMG: Project Management Group
DMC: Data Monitoring Comittee
